### The specific objectives are

#### Phase 1

To adapt the “CEQ 2.0” and “SCIB” scales to the Iranian context and determine their psychometric properties.To measure the childbirth experience score among primiparous women who gave birth in public and private hospitals of Tabriz, Iran.To determine perceived support and control in birth among primiparous women.To determine the relationship between perceived support and control in birth with childbirth experience among primiparous women.To determine the relationship between sociodemographic characteristics and childbirth experience among primiparous women.To determine the relationship between antenatal, intrapartum factors and childbirth experience among primiparous women.

#### Phase 2

7.To explore women’s perceptions regarding the aspects and determinants of childbirth experience among primiparous women.

#### Phase 3

8.To develop an evidence-based guideline to improve women’s childbirth experience by meeting their needs and expectations.

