## Methods/ design

### Study design

The present study will use a mixed method with an explanatory sequential approach. The paradigm of the mixed method is based on the principle of pragmatism. Based on this paradigm, the mixed use of quantitative and qualitative approaches leads to a better understanding of the problem [29, 30].

The sequential explanatory design is a mixed method that firstly collects and analyses quantitative data and then qualitative data to explain and/or generalise quantitative data. In this model, the researcher first identified quantitative data that required further explanation and then collected qualitative data from participants, who could contribute to a deeper explanation of the collected data [30].

This study will have three phases. Phase one is divided to two sections: the aim of first section is to adapt the scales to the Iranian context and determine their psychometric characteristics. The second section is a descriptive-analytic cross-sectional study to identify the women’s childbirth experiences and influencing factors (socio-demographic, antenatal, and intrapartum factors). Phase two is an exploratory qualitative study to explore women’s childbirth experiences in more detail. Phase three is about developing an evidence based and culturally sensitive guideline based on literature review, the results of phase one and two and experts’ opinion using the Delphi method (Fig. 1).

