### Phase one: quantitative study

A descriptive-analytic cross-sectional study will assess childbirth experiences and its relationship with support and control in birth, sociodemographic, antenatal and intrapartum factors among the participants. The target population will be primiparous women who give birth in public and private hospitals in Tabriz, Iran. Childbirth Experience Questionnaire 2.0 (CEQ 2.0) and Support and Control in Birth (SCIB) scales will be used to collect the data. The data collection tools will be validated and standardized for use among the Iranian population.

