#### Data analysis

The data obtained in the first section of phase one will be analyzed using SPSS Statistics Version 25.0 for Windows (IBM Inc., Armonk, NY, USA). In the cross sectional stage, descriptive statistics will be used to describe the socio-demographic, antenatal and intrapartum factors and childbirth experience. The analytical statistics including univariate will be used to test the correlation between socio-demographic, antenatal and intrapartum variables with the childbirth experience. Then, variables with a correlation of *p* < 0.1 in the univariate analysis will be entered into the multivariable logistic model. All tests will be two-tailed. *P*-value <0.05 will be considered statistically significant. To promote data quality in the cross sectional stage, procedures such as double data entry and range checks for data values will be conducted.

The data obtained in the second section of phase one will be analyzed using SPSS Statistics Version 25.0 for Windows (IBM Inc., Armonk, NY, USA) and AMOS software. Construct validity will be measured using exploratory factor analysis and confirmatory factor analysis. In exploratory factor analysis, the Principal Axis Factoring method and oblimin rotation will be used to extract and rotate the factors. If the items loading are lower than 0.3, the item may be removed [37]. Next, exploratory analysis, confirmatory factor analysis will be used to support the findings of the scale dimensions. Indicators with acceptable values for the model to be approved include Root Mean Square Error of Approximation (RMSEA) < 0.08, Goodness of Fit Index (GFI), Comparative Fit Index (CFI) ≥ 0.90, and Normed chi-square ( x^2^/df < 5). Internal consistency will be assessed using the Cronbach’s Coefficient alpha. The test-retest reliability will be calculated through test-retest of 20 primiparous mothers with a 2 week interval and the calculation of Intra Correlation Coefficient (ICC).

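### A univariate p < 0.1 screen is the only stated route into the multivariable model and can drop masked effects; SCIB, the exposure of objective 4, has no stated analysis

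*Protocol article*

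**What the plan says.** Three parts of the protocol article bear on this.

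- **Data analysis (phase one), entry rule.** "Then, variables with a correlation of *p* < 0.1 in the univariate analysis will be entered" into a multivariable logistic model. No forced-in or pre-specified covariates are named.
- **Data analysis (phase one), variables.** The univariate step "will be used to test the correlation between socio-demographic, antenatal and intrapartum variables with the childbirth experience". For description, "descriptive statistics will be used to describe the socio-demographic, antenatal and intrapartum factors and childbirth experience". SCIB appears in neither list. The section's other paragraph covers only the psychometric work.
- **Objectives and design.** Objective 4 reads "To determine the relationship between perceived support and control in birth with childbirth experience among primiparous women" and stands apart from objectives 5 (sociodemographic) and 6 (antenatal and intrapartum). Under Phase one: quantitative study, the survey is to assess childbirth experience and "its relationship with support and control in birth, sociodemographic, antenatal and intrapartum factors among the participants", so support and control is again a group of its own. Study design, by contrast, speaks of "influencing factors (socio-demographic, antenatal, and intrapartum factors" and leaves it out.

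**The concern.** There are two defects.

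**The screen.** A crude p-value shows neither whether a variable confounds another nor whether it has an effect after adjustment. If a factor pushes the score one way and is correlated with a factor that pushes it the other way, its crude association can be close to zero. It then fails p < 0.1 and never reaches the model that would have shown its effect. The p-values and intervals from the final model also read as if its terms had been fixed in advance.

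**SCIB.** The analysis list conflicts with the objectives. Support and control is a separate exposure in objective 4 and in the design statement, so it cannot simply be read as one of the intrapartum variables, yet no analysis is named for it. Where it goes also matters. SCIB asks about pain relief, decisions and procedures, so it may lie downstream of induction, augmentation, epidural analgesia and immobilization. If everything went into one model, the intrapartum coefficients would be adjusted for something they may act through.

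At stake are the answers to objectives 4 to 6. Phase one findings also help to shape the interview questions and are integrated with the qualitative results into recommendations for the Delphi panel.

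**Working it through.** **Plan's own figure.** 10 per item × 33 items = 330; × design effect 2 = 660; 660 × 1.20 = 792, which rounds to the stated 800. (Dividing by 0.80 gives 825; nothing below depends on the difference.) After 20% loss, 800 × 0.80 = 640 women remain, an effective 640 / 2 = 320.

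**Why masking defeats the screen.** With two standardised factors, adjusted effects b1 and b2 and correlation ρ, the crude effect of the first is b1 + ρ·b2. All effect sizes and correlations below are assumptions; the document gives none.

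*Linear example.* b1 = 0.2, b2 = −0.2, ρ = 0.7.
- Crude effect = 0.2 − 0.7 × 0.2 = 0.06.
- Screen at n = 320: z = 0.06 × √320 / √(1 − 0.0036) = 1.08, so the chance of p < 0.1 is 29%. At n = 640 it is 45%.
- Adjusted model: R² = 0.04 + 0.04 − 2 × 0.7 × 0.04 = 0.024. At n = 320, z = 0.2 × √(320 × 0.51) / √0.976 = 2.59, so power at p < 0.05 is 73%. At n = 640 it is 96%.

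*Logistic simulation, matching the planned model.* Two standard-normal predictors, about 50% prevalence, 1000 runs per setting, adjusted OR 1.5 per SD for the factor of interest. Sizes are n = 660 and n = 660 / 2 = 330 (design effect 2). A run counts as lost if the adjusted p is < 0.05 but the screening p is ≥ 0.1.

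| n | OR of second factor | ρ | Passes screen | Adjusted power | Lost |
|---|---|---|---|---|---|
| 660 | 1 (no effect) | 0 | 100% | 99.9% | 0% |
| 660 | 2 | −0.3 | 77.6% | 99.7% | 22.1% |
| 660 | 3 | −0.3 | 19.1% | 99.6% | 80.7% |
| 660 | 3 | −0.4 | 10.5% | 99.0% | 89.5% |
| 330 | 1 (no effect) | 0 | 98.0% | 94.8% | 0% |
| 330 | 2 | −0.3 | 51.3% | 89.3% | 38.0% |
| 330 | 3 | −0.3 | 15.4% | 87.6% | 73.3% |
| 330 | 3 | −0.4 | 9.2% | 86.0% | 81.9% |

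The pattern follows the formula. On the log-odds scale ln 1.5 = 0.405. The masking term is 0.3 × ln 2 = 0.208, 0.3 × ln 3 = 0.330 or 0.4 × ln 3 = 0.439. The crude effect that remains is about 0.197, 0.075 or −0.034 (approximate for a logistic model). In the last setting the factor passes about as often as a pure noise variable would, 10%.

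**How many terms the data can carry.** Take 30 terms as an example. A linear model has 640 / 30 = 21 women per term, or 320 / 30 = 10.7 after the design effect. In a logistic model the smaller outcome group is the limit. At best, with a 50:50 split, that is 320 / 30 = 10.7 per term before any design effect, and fewer with an uneven split. The document gives no event count.

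**SCIB.** No arithmetic applies. Objective 4 and the design statement name it separately; the descriptive and univariate lists do not name it.

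**The case against.** The strongest reply is that this is a condensed article on an exploratory survey. A threshold of 0.1 is liberal and openly stated, the wording on analytical statistics is not exhaustive, and a simple correlation would answer objective 4. Part of this stands.

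- A reader might infer that objective 4 will go unanswered. The document does not support that: SCIB is collected, and the design statement commits to assessing its relationship with childbirth experience. What is missing is a stated analysis. Condensation does not fully explain the gap, because the section gives an explicit variable list that conflicts with the objectives.
- A reader might infer that the screen generally discards real effects. It does not. Without a correlated masking factor it lost nothing in the simulation, and the masking settings are assumptions, some of them strong.
- A reader might infer that the sample is large enough to enter any number of terms. That holds only for a linear model with the design effect ignored; the plan states a logistic model.
- The risk factors listed in the Background might look like a ready-made covariate set. They are not. Previous negative birth cannot apply to primiparous women, major pregnancy complications are largely excluded, fear of childbirth is not among the listed measures, and perceived support and control is SCIB itself.
- The effect on later phases is diluted. Interviewees are chosen by extreme childbirth experience scores, interview questions also draw on the literature, and the guideline adds a literature review and expert opinion.
- That SCIB lies downstream of intrapartum events is plausible from its content, but the document does not state it.

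None of this removes the two defects: an entry rule that is a poor basis for adjusted inference, and an objective with no analysis attached.

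**Conclusion.** The concern holds in a limited form. The p < 0.1 screen is the only stated way into the model. It can remove a factor with a real adjusted effect, and it leaves final p-values and intervals that take no account of the selection. Under the assumed masking settings the loss was 22.1% to 89.5% of runs at n = 660 and 38.0% to 81.9% at n = 330; without masking it was zero. Which case applies cannot be known from the document, because it gives no correlations or effect sizes.

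Separately, and without any assumption, objective 4 has no stated analysis, because the section's variable list leaves out an exposure that the objectives and the design statement treat as distinct. Both should be corrected before analysis. Neither invalidates the study, since the data needed are already to be collected.

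**What to change.** 1. Remove the p < 0.1 screen. Choose covariates in advance on subject-matter grounds from the socio-demographic, antenatal and intrapartum variables that the study actually collects and that apply to low-risk primiparous women. Enter them all. If the logistic model is kept, limit the number of terms by the size of the smaller outcome group.
2. Fit **model A** with these covariates, for objectives 5 and 6.
3. Fit **model B** as model A plus the SCIB subscales, for objective 4. Intrapartum effects are then also reported without adjustment for perceived support and control.
4. Report SCIB against each subscale of the Childbirth Experience Questionnaire (CEQ), and note the content overlap when interpreting it. SCIB support overlaps CEQ professional support (information and care by staff). SCIB internal control (emotions, pain) overlaps CEQ own capacity (feelings about childbirth and labor pain).
5. Name SCIB in the descriptive and analytical variable lists so that they agree with the objectives.

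The cost is a change of wording, one extra model, and somewhat wider intervals from retaining weak covariates. No new data are needed.

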#### Scales and data collection

Quantitative data are collected using sociodemographic and obstetric characteristics questionnaires, CEQ 2.0 and SCIB by a research staff member and collected in person. Sociodemographic and obstetric questionnaires will include questions on age, spouse’s age, and medical interventions during labor such as induction and augmentation, epidural analgesia, immobilization in labor.

The second version of CEQ contained 23 items and measures the women’s perceptions of first labour and birth, and includes the following subscales: own capacity (personal feeling about childbirth and labor pain), professional support (information and midwifery care), perceived safety (sense of safety and childbirth memories), and participation (the person’s ability to change childbirth situation). The CEQ consists of 20 items in the form of multiple-choice questions and three items completed using Visual Analog Scale (VAS). Participants will be asked to rate their level of agreement or disagreement with each item by using a 4 point Likert scale where 1 = totally agree; 2 = mostly agree; 3 = mostly disagree; and 4 = totally disagree. Questions answered in the VAS form will be changed from a 0–100 score to 1–4 score where scores 0–40 = score 1, scores 41–60 = score 2, scores 61–80 = score 3, and scores 81–100 = score 4. Statements with negative concepts (experiencing severe pain, feeling tired, scared and having a bad memory) are scored in reverse. Higher mean scores reflect more positive childbirth experiences. The overall Cronbach’s alpha of the original CEQ has not been reported. However, the Cronbach’s alpha for own capacity, participation, perceived safety, and professional support subscales has been reported 0.82, 0.62, 0.78, and 0.88 respectively [34]. This tool will be completed at least 1 month after childbirth.

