#### Sample size and sampling method

Purposeful sampling will be used in phase two. The participants in this phase will be selected based on the mean total score of childbirth experience, which is collected in phase one of the study. Women with 10% upper and lower scores of childbirth experience will be selected as the extreme cases. We will seek to interview women with either a positive or negative childbirth experience to collect more comprehensive information about their childbirth experience and its effective factors.

The analysis process will be initiated from the first interview. The aim is to clarify the details and relationships between the pivotal concepts and categories derived from investigating the initial data. In this way, the selection of the participants will continue until the relationships between research concepts and variables, i.e. theoretical saturation, are determined [38]. In this study, the sampling will continue until the researcher felt no further information will be collected during data analysis and coding. Nevertheless, some references estimated 12 participants as the minimum number of participants required for a qualitative study [39].

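### The adjusted predictor analysis is a logistic model, but the outcome is defined only as a mean score and no event or cut-off is given

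*Protocol article*

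**What the plan says.** The Phase 1 objectives include "To measure the childbirth experience score among primiparous women who gave birth in public and private hospitals of Tabriz, Iran". Later objectives in the same list relate support and control, sociodemographic, antenatal and intrapartum factors to childbirth experience.

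Phase one, Scales and data collection, describes the measure: 23 items, each ending on a 1 to 4 scale, summarised as a mean. It adds that "Higher mean scores reflect more positive childbirth experiences". No threshold separating positive from negative experience is given there. The Phase two section on sample size and sampling also works from the mean total score.

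Phase one, Data analysis, sets out two steps for the cross-sectional stage. Univariate methods "will be used to test the correlation between socio-demographic, antenatal and intrapartum variables with the childbirth experience". Variables with a univariate p-value below 0.1 are then "entered into the multivariable logistic model". The same paragraph fixes the test conventions: "All tests will be two-tailed", and a p-"value <0.05 will be considered statistically significant". It does not say whether the logistic model is binary or ordinal.

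The only cut on the score is in Phase two: "Women with 10% upper and lower scores of childbirth experience will be selected as the extreme cases". That rule chooses interviewees. It does not define an outcome for the regression.

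**The concern.** A binary logistic model needs a yes/no outcome. The article offers only a score: 23 items scored 1 to 4 give totals from 23 to 92, so up to 92 - 23 + 1 = 70 distinct values. To run a binary model, someone must decide what counts as the event, and the article does not say what that is or when it is decided.

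This is the only adjusted analysis of predictors in Phase one. Its findings feed the interview questions (Phase two, Data collection) and the recommendations put to the Delphi experts (Phase three). If the cut stays open, the list of factors reported as predictors can change with the cut. Splitting a score also usually discards information, so real associations are easier to miss. The sample size was not set with this model in mind, so no margin is built in for that loss.

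**Working it through.** **1. The plan's own figure.** Phase one, Sample size and sampling method: 33 SCIB items × 10 per item = 330; × design effect 2 = 660; × 1.20 for attrition = 792, rounded up to 800. (Dividing instead, 660 / 0.80 = 825.) The 800 therefore follows from a factor-analysis rule with a 20% uplift. It claims no power for the regression. I use 660 below because it is the number planned before the attrition allowance.

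**2. Model against outcome.**

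| Place | What is fixed |
|---|---|
| Phase 1 objectives | a childbirth experience score |
| Scales and data collection | a mean score, higher is better, no threshold |
| Data analysis, univariate step | correlation with childbirth experience |
| Data analysis, multivariable step | logistic model, event not stated |
| Phase two sampling | top and bottom 10%, for interviews only |

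Nothing links the score to a category.

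**3. Information kept by a binary split.** The documents give no SD, distribution, effect size or event proportion, so this step rests on assumptions: a normal score and small effects. Relative to linear regression on the score, a split at proportion p keeps φ(z_p)² / [p(1 - p)].

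| Cut p | Kept | Lost | 660 act like | n needed to match 660 analysed linearly |
|---|---|---|---|---|
| 0.50 | 0.637 (2/π) | 36% | 420 | 1,037 |
| 0.30 | 0.576 | 42% | 380 | 1,147 |
| 0.25 | 0.539 | 46% | 355 | 1,226 |
| 0.20 | 0.490 | 51% | 323 | 1,348 |

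Example at the quartile: φ(0.674) = 0.3178; 0.3178² / (0.25 × 0.75) = 0.1010 / 0.1875 = 0.539. These counts are before any design effect. A design effect would reduce a linear analysis too, so it is not a cost of splitting.

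**4. Check by simulation.** The settings were one normal predictor, no clustering, 1,500 runs, two-sided 0.05 and N = 660. The correlation was set for about 80% power in the linear model: r = tanh[(1.960 + 0.842) / √657] = 0.109. Power was 79.5% for the linear model. For binary logistic it was 61.2% (median), 54.6% (30%) and 48.1% (20%), which agrees with step 3.

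**5. Sensitivity to score shape.** For a general density f, the loss at cut q is 1 - f(q)² × variance / [p(1 - p)]. At the median:

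- t with 5 degrees of freedom: 4%
- logistic: 18%
- normal: 36%
- left-skewed beta(5,2): 45%

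A flat (uniform) score would give 67%, but that shape is unlikely for a mean of 23 items. At a 20% cut the four single-peaked shapes lose between 41% (t) and 68% (beta).

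**6. Ordinal alternative.** An ordinal logistic model on the ordered score needs no cut. For a normal score it keeps about 3/π = 0.955, a loss of about 5%.

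**The case against.** The best defence is that the article condenses a fuller protocol or analysis plan. A cut-off may be fixed there, the model may be ordinal, or the word logistic may be a slip for linear. On any of these readings part of the cost disappears. This defence limits several stronger conclusions that a reader might draw:

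- **That the plan forces a cut chosen after seeing the data.** It does not. A cut could be fixed in advance, for example at a scale midpoint, and an ordinal model needs none. The article leaves the matter open.
- **That a third or more of the information is certain to be lost.** This holds only for a binary split of a roughly normal score with small effects. With heavier tails the median-split loss is much smaller.
- **That the interview rule implies a 10% cut for the model.** Nothing connects the two.
- **That every Phase 1 objective concerns this score.** The first is scale adaptation and the third is perceived support and control.
- **That screening and final models analyse different outcomes.** The univariate sentence refers to childbirth experience without naming the score, so this is an inference.
- **That the 800 is wrong because of the model.** It comes from a different rule and claims nothing about regression power.

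The mismatch survives all of this. The article chose to state the model, the entry threshold, the significance level and the sidedness. As stated, the model does not fit the outcome as defined. A later cut-off would turn a score into a category that the article nowhere describes. This is more than a detail left for elsewhere.

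**Conclusion.** The point holds as a mismatch between model and outcome: a logistic model is named for an outcome defined only as a mean score, with no event, category or cut-off. That part rests on the text alone.

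The size is conditional. If the score is split in two and is roughly normal with small effects, the loss is at least 36% (median) and 46% at a quartile, so the planned 660 women act like about 420 and 355. The score distribution is an assumption throughout. If the model is ordinal, the loss is about 5% and the defect is mainly one of wording. No stated figure in the plan is contradicted.

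**What to change.** In Phase one, Data analysis, make multivariable linear regression on the CEQ 2.0 mean score the main predictor analysis. Report adjusted mean differences with 95% confidence intervals, and allow for the health-centre clusters through which women are sampled. Name the same score as the outcome of the univariate step.

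If odds ratios are wanted, add a logistic model as secondary. State whether it is binary or ordinal and, if binary, give the event and a justified cut-off fixed before data are seen. Stating these for the existing model would also cure the mismatch, but a binary split would usually still lose information.

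The cost is a few sentences of analysis wording and no new data. The small downside is that the main results appear as mean differences rather than odds ratios.

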#### Sample size and sampling method

According to Nunnally & Bernstien, for a factor analysis in the validation of scales, 10 samples per item are required [31]. Given the 33 items in SCIB, 330 samples are needed. However, a sample of 660 people is required due to the sampling plan and the design effect of 2. Considering that the sampling plan in the first phase is cluster, the design effect must be considered. “The loss of effectiveness by the use of cluster sampling, instead of simple random sampling, is the design effect” [28]. Using a cluster sample usually needs a larger sample size than a simple random sampling and for a well-designed study, the design effect usually ranges from 1 to 3 [32, 33]. Considering a minimum 20% attrition rate, the total required sample size is calculated to be a minimum of 800 participants.

First, the rate of vaginal childbirth in public and private hospitals will be extracted separately. Then, all of the urban and suburban Tabriz health centers will be listed and numbered (114 centers). Using cluster sampling and the website www.random.org, approximately half of the centers will be randomly selected. A list of potential participants will be arranged based on the health records at each selected center. From the list, the required sample size for each center will be determined using the proportional sampling method by the rate of vaginal childbirth in public and private hospitals and the samples will be randomly selected. Using the phone number registered in each record, the researcher will call the potential participants and invite them to participate in the study.

The eligible participants will be provided with full explanations about the study objectives and procedures. Socio-demographic questionnaire, Childbirth Experience Questionnaire 2.0 (CEQ 2.0), and Support and Control in Birth questionnaire (SCIB) will be filled out in a relatively quiet environment by a research staff member and collected in person. A number of participants are likely to be illiterate, so the questionnaires will be completed by the researcher in order for the data collection method to be the same for all individuals. Obstetrics information will be collected by referring to individuals’ medical records. Also, informed consent will be obtained before collecting information from women’s medical records.

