SCIB contains 33 items and its subscales include internal control, external control, and support. The internal control contains 10 items that focus on the emotions, behavior, pain, and physical functioning (e.g. “I overcame my pain”). The external control contains 11 items that focus on pain relief, information, environment, decisions and procedures, and birth outcome (e.g. “I had control over when procedures happened”). The support contains 12 items that focus on coping methods, staff attitude, empathy and understanding, encouragement, listening, informational support, and support with pain relief (e.g. “The staff dismissed things I said to them”). Questions are scored on a 5-point Likert scale from agree completely to disagree completely. A score of 1 shows less control and support, and a score of 5 shows more control and support. Ten items are scored in reverse. SCIB will be completed 1 month after childbirth. The overall Cronbach’s alpha of the original SCIB has been reported 0.95. Also, the Cronbach’s alpha for internal control, external control, and support subscales has been reported 0.86, 0.93, and 0.93 respectively [21].

Due to the fact that the CEQ 2.0 and SCIB have not been validated in Iran, they will be standardized and validated prior to the start of the main study. The scales will be translated into Farsi using the Forward & Backward Translation method. The translated versions will be edited by two experts in concepts and the final versions will be created. For quantitative valuation of face validity, 20 postpartum mothers will complete the face validity checklist and will be asked to comment on clarity, simplicity, and relevance of items. Based on these notes, the translated items will be revised. The mothers will also be requested to comment on the impact score of the items on a 4-point Likert scale. To obtain the impact score, the percentage of mothers who score the items a value of 4 will be multiplied by the mean total impact score. Impact scores greater than 1.5 will be considered satisfactory [35].

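### The confirmatory factor analysis supports a structure the exploratory analysis has just selected, with one sample sized for one factor analysis, so it is not an independent test

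*Protocol article*

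**What the plan says.** The protocol article sets the following for phase one.

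- **Methods (Data analysis).** "Construct validity will be measured using exploratory factor analysis and confirmatory factor analysis". The EFA uses principal axis factoring with oblimin rotation, and "If the items loading are lower than 0.3, the item may be removed". Then: "Next, exploratory analysis, confirmatory factor analysis will be used to support the findings of the scale dimensions". The CFA is judged by RMSEA below 0.08, GFI and CFI of at least 0.90, and chi-square/df below 5.
- **Sample (Sample size and sampling method).** The rule is that "for a factor analysis in the validation of scales, 10 samples per item are required". Applied to the longer of the two scales, this becomes: "Given the 33 items in SCIB, 330 samples are needed". The cluster sampling then doubles the figure to 660. Losses are added last: "Considering a minimum 20% attrition rate, the total required sample size is calculated to be a minimum of 800 participants".
- **Known structure (Scales and data collection).** CEQ 2.0 has 23 items in four named subscales. SCIB has 33 items in three subscales of 10, 11 and 12 items.
- **Timing (Scales and data collection).** Because neither scale has been validated in Iran, "they will be standardized and validated prior to the start of the main study".
- **Use of the 800 (Abstract, Methods/design).** The same number of primiparous women is to be selected to measure childbirth experience and its predictors.
- **Phase two (Sample size and sampling method).** Interviewees come from the upper and lower 10% of the phase-one childbirth experience score.

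**The concern.** An EFA fits the sample it is given, chance correlations included. If the chosen factors and retained items are then put through a CFA on the same women, the fit limits are applied to a model tuned to those data. Passing is weaker evidence of construct validity than the word confirmatory suggests.

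Both instruments arrive with a published structure. That is the natural prior hypothesis for a translated scale, yet the plan ties the CFA to the EFA's findings and does not say that it tests the published subscales.

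The outcome is also affected. The women whose data would validate the scales appear to be the survey sample, and the plan does not say which item set is scored if the EFA removes CEQ items. A change there would alter the phase-one outcome after the data are seen, and with it the extreme groups from which phase two recruits.

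**Working it through.** **1. Reproduce the plan's sample size.**

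- Items × 10: 33 × 10 = 330.
- Design effect 2: 330 × 2 = 660.
- Attrition 20%: 660 × 1.20 = 792, which rounds up to the stated 800. (Dividing gives 660 / 0.80 = 825.)

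The figure is reproduced, and it covers one factor analysis. The other groups in the validation are 20 mothers for face validity, 10 experts for content validity and 20 mothers for test-retest. None could carry a CFA.

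**2. What separate EFA and CFA samples would need under the plan's own rule.**

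- Analysed: 2 × 660 = 1,320.
- Recruited: 1,320 × 1.20 = 1,584, or 1,320 / 0.80 = 1,650.

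**3. What a split of the planned sample would give.**

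- 800 × 0.80 = 640 analysed, or 320 per half.
- Nominal: 320 / 33 = 9.7 per SCIB item and 320 / 23 = 13.9 per CEQ item.
- After the design effect of 2: 320 / 2 = 160 effective, so 160 / 33 = 4.8 per SCIB item and 160 / 23 = 7.0 per CEQ item.

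**4. Size of the optimism.** The documents give no loadings, so this rests on assumed populations: 33 items in three factors of 10, 11 and 12; main loadings 0.6; factor correlation 0.4; normal, unclustered data. In each run, EFA with oblimin extracted three factors, items loading below 0.3 were dropped and each remaining item went to its highest loading. A maximum-likelihood CFA was then fitted to the same data and to a fresh sample of equal size. Passing means meeting the CFI, RMSEA and chi-square/df limits; GFI was not computed. There were 40 replicates per cell for the clean and heavy-misfit rows and 80 for the near-limit rows.

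| Assumed structure | n | Mean CFI, same data | Mean CFI, fresh data | Pass, same | Pass, fresh |
|---|---|---|---|---|---|
| Clean | 330 | 0.991 | 0.990 | 100% | 100% |
| Clean | 640 | 0.997 | 0.996 | 100% | 100% |
| 9 cross-loading items, minor-factor SD 0.06 | 330 | 0.900 | 0.880 | 46% | 12% |
| 9 cross-loading items, minor-factor SD 0.06 | 640 | 0.898 | 0.883 | 50% | 6% |
| 9 cross-loading items, minor-factor SD 0.12 | 330 | 0.741 | 0.730 | 0% | 0% |
| 9 cross-loading items, minor-factor SD 0.12 | 640 | 0.749 | 0.734 | 0% | 0% |

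Over all cells run, including n = 165 and 16 cross-loading items, mean CFI was higher on the same data by about 0.001 to 0.04. In the near-limit rows mean RMSEA stayed between 0.045 and 0.049, so CFI decided the result. The Monte Carlo standard error of the 50% is √(0.5 × 0.5 / 80) = 0.056 and of the 6% is √(0.06 × 0.94 / 80) = 0.027, so that contrast is not simulation noise.

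**5. What the quoted reliabilities suggest about loadings.** With equal loadings, mean inter-item correlation is r = α / (k − α(k − 1)) and the loading is √r. The original SCIB alphas give:

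- Internal control: 0.86 / (10 − 7.74) = 0.38, loading 0.62.
- External control: 0.93 / (11 − 9.30) = 0.55, loading 0.74.
- Support: 0.93 / (12 − 10.23) = 0.53, loading about 0.72.

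The main loading of 0.6 assumed above is close to the lowest of these. Alpha says nothing about cross-loadings or minor factors, which drive the near-limit rows.

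**6. Timing.** Scales and data collection places validation before the main study. Sample size and sampling method derives the 800 from the needs of scale validation, and the Abstract gives the same 800 as the survey sample. No separate validation cohort is described. Study design calls adaptation of the scales the first section of phase one and the survey the second; Data analysis labels them the other way round.

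**The case against.** A reader might infer that a CFA on the same women cannot fail. The simulations contradict this. A CFA fixes at zero the cross-loadings that an EFA leaves free, and with heavy misfit none of the same-data runs passed. The defect is lack of independence, not a foregone result.

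Nor can the optimism be called large. A separate check with simple structure (assumed factor correlation 0.3) gave CFI of 0.969 on the same data against 0.968 on new data at loadings of 0.4, and 0.984 on both at 0.5. The original SCIB alphas point to loadings higher still. Nothing in the documents shows that the Farsi scales fall in the middle band where the verdict changes. This stands, and it limits the claim about size.

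The article does not state that EFA and CFA use the same women, and how records are divided may be left to a fuller document. The sentence on the CFA is also garbled, and its scale dimensions could mean the published subscales. This stands in part. But the stated sequence has the CFA support what precedes it, and the sample was not sized for two analyses.

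A reader might also infer that the outcome will be redefined. The article says only that an item may be removed and describes a 23-item CEQ; it nowhere says that a shortened version becomes the survey outcome. The valid point is that this is left open.

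Finally, starting with EFA in a new language and culture is defensible. That argues for keeping EFA available, not for calling what follows it confirmation.

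**Conclusion.** The concern holds in limited form. As written, the CFA checks a structure and item set chosen by the EFA on the only data described, so it is not an independent test of construct validity. Its fit indices are biased upward. The direction was the same in all the cross-loading scenarios; the amount depends on unknown loadings and misfit, from essentially nil with a clean structure to about 0.04 in CFI in the worst cell. It changes the conclusion only when fit is near the stated limits.

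That the same women serve both analyses is an inference from the single-analysis sample size and the absence of any split, not a statement in the article. The order of validation and main study is a separate contradiction within the document. The point deserves action because a better sequence is available without enlarging the sample.

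**What to change.** 1. **Test the published structures first.** Run the CFA of the four-factor CEQ 2.0 and three-factor SCIB on the full sample, with items allocated as in the source instruments, against the limits already stated.
2. **Use EFA only if that fails.** Either label the resulting structure exploratory, or cross-validate it with EFA on a random half of the health centres and CFA on the other half. Splitting by centre respects the cluster sampling. State that each half has about 320 women, about 160 effective, or 4.8 per SCIB item.
3. **Fix the outcome.** Name the full 23-item CEQ 2.0 score as the phase-one outcome and the basis for phase-two selection. Use any shortened version as a sensitivity analysis only.
4. **Reconcile the timing.** Either describe a separate, earlier validation sample with its size, or say that validation and survey share the 800 and remove the claim that validation comes first. Align the section labels in Study design and Data analysis.

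**Cost.** Items 1 and 3 change wording only and need no extra women, as does item 4 if the shared sample is acknowledged. A split under item 2 falls to about half of the plan's 10-per-item rule for SCIB once clustering is counted. Keeping that rule in both halves would need 1,320 analysed women, so the split should be a fallback with its precision stated.
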